**Alcohol consequences**				
	T1, T2, T3, and T4	PROMIS Short Form–Alcohol Use–Negative Consequences 7a [41]	Exploratory	7 items that assess the negative consequences of using alcohol in the previous 30 days (eg, unreliability, social problems, and judgment)
	T1, T2, T3, and T4	PROMIS Short Form–Alcohol Use–Positive Consequences 7a [41]	Exploratory	7 items that assess the positive consequences of using alcohol in the previous 30 days (eg, self-esteem, confidence, and enjoyment)
**Alcohol expectancies**				
	T1, T2, T3, and T4	PROMIS Short Form–Alcohol Use–Negative Expectancies 7a [41]	Exploratory	7 items that assess the negative expectancies of alcohol use (eg, making bad decisions and behaving rudely)
	T1, T2, T3, and T4	PROMIS Short Form–Alcohol Use–Positive Expectancies 7a [41]	Exploratory	7 items that assess the positive expectancies of alcohol use (eg, improves mood and sociability)
Readiness to change drinking, T1, T2, T3, and T4		Readiness to Change Questionnaire [42]	Exploratory	12 items that assess the stage of change toward reducing alcohol use (precontemplation, contemplation, and action)
Drinking refusal self-efficacy, T1, T2, T3, and T4		Drinking Refusal Self-Efficacy Questionnaire–Revised [43]	Exploratory	19 items that assess individuals’ belief in their ability to resist alcohol, with 3 subscales: social pressure drinking, emotional relief drinking, and opportunistic drinking
Sexual risk behaviors, T1, T2, T3, and T4		National HIV Behavioral Surveillance System [44]	Exploratory	≥6 items: number of partners in previous 12 (T1) or 3 (T2-T4) months; partner type (main vs casual); partner HIV status; frequency of condomless sex (anal, vaginal, or oral), transactional sex, and concurrent sex and drug or alcohol use; and PrEP use
Condom attitudes, T1, T2, T3, and T4		Multidimensional Condom Attitudes Scale [45]	Exploratory	16 items that measure attitudes toward condoms across 7 factors: reliability, effectiveness, pleasure, identity stigma, embarrassment about purchase, negotiation, and action maintenance
Perceived HIV risk, T1, T2, T3, and T4		Perceived Risk of HIV Scale [46]	Exploratory	8 items that assess likelihood estimates, intuitive judgments, and salience of HIV risk based on previous behaviors
Discrimination due to sexual or gender identity, T1, T2, T3, and T4		Heterosexist Harassment, Rejection, and Discrimination Scale [47]	Exploratory	12 items that assess harassment, rejection, and family discrimination related to LGBTQ^h^ identities
Alcohol cravings, T1, T2, T3, and T4		Penn Alcohol Craving Scale [48]	Exploratory	5 items that assess alcohol-related cravings; higher scores indicate higher rates of alcohol cravings
Alcohol Use, T1, T2, T3, and T4		Alcohol Quantity Measures	Exploratory	7 items that assess alcohol use over the past 30 days

^a^T1: baseline assessment.

^b^T3: 6-month assessment.

^c^T4: 9-month assessment.

^d^AWSC: alcohol withdrawal symptom checklist.

^e^PrEP: pre-exposure prophylaxis.

^f^T2: 3-month assessment.

^g^PROMIS: Patient-Reported Outcomes Measurement Information System.

^h^LGBTQ: lesbian, gay, bisexual, transgender, and queer.

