## Methods

### Study Design

We will conduct a 3-arm RCT of TRAC and TRAC-ER (n=405 HIV-negative SMMT individuals; n=135, 33% per arm), with the following conditions: (1) SAM-only comparison group, (2) SAM+TRAC (no EMI messaging), and (3) SAM+TRAC-ER (participants receive EMI messaging when visiting risky locations).

Breathalyzer results and daily self-reports will be used to assess the primary and secondary outcomes of drinking days, drinks per drinking day, binge drinking episodes, and HIV risk behaviors. Additional assessments at baseline (T1), 3 months (T2), 6 months (T3), and 9 months (T4) will evaluate exploratory long-term outcomes, including diagnoses of HIV or other sexually transmitted infections (STIs).

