#### Description of Study Arms

##### Overview

Participants will be enrolled in the study for 9 months, including the 2-month intervention period and multiple follow-up monitoring periods to assess long-term effects. All participants will begin with a 30-day monitoring period, which will establish baseline alcohol use through daily breathalyzer reading requests and surveys. After this 30-day period, they will complete additional baseline measures (T1) and then begin their assigned intervention, if applicable. After the interventions are delivered, participants will complete an additional self-report (T2). Subsequently, there will be 2 additional monitoring periods and assessments spread across the 9-month study period to assess long-term intervention effects, with some months involving no study activities. A depiction of the participation timeline is included in Figure 2, and details of study activities completed across the study timeline and RCT arms are provided in Table 1.

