##### Data Analysis Plan

###### Analysis of Alcohol Use Outcomes

Descriptive statistics for breathalyzer reading data will be summarized overall, by group (SAM only, SAM+TRAC, and SAM+TRAC-ER) and across time periods (T1-T4). The primary outcome is the number of drinking days in the past month, which is defined as the days on which individuals did not report 2 negative breathalyzer results. The rate of drinking (incidence of drinking) is the number of drinking days observed within the past month. The secondary outcomes include the number of drinks per drinking day, the number of days with binge drinking episodes, and the number of days for which HIV risk behaviors occur. All these outcomes are count data. The goal of this analysis is 2-fold: first, short-term analysis at the end of the 2-month intervention period, and, second, long-term analysis at the end of 9 months. We will fit a generalized linear model [50], with a general formulation for count data as follows:

g(E(y_i_)) = g(μ_i_) = x'_i_β (1)

where *y_i_* is the outcome variable for (*i*=1,2,3,...,*n*), *n* is the total number of observations, *μ*_i_=*E*(*y_i_*) is the expected count, *g* is the link function (a mathematical function connecting the counts with the explanatory variables), *β* is a vector of regression parameters to be estimated, and *x_i_* is a vector of independent covariates to be included in the model. These covariates include group, time, age (or age group), gender identity, sexual orientation, and site.

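### In the exploratory T1–T4 battery, the partner count is recalled over 12 months at T1 and 3 months afterwards, so about a third of the T2 window precedes the intervention and change from T1 cannot be read

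*Protocol article*

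**What the plan says.** The sexual risk behaviors row of Table 2, labelled exploratory, gives the recall as "number of partners in previous 12 (T1) or 3 (T2-T4) months".

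The visit schedule is in the Overview of the study arms. The run-in comes first: "All participants will begin with a 30-day monitoring period, which will establish baseline alcohol use through daily breathalyzer reading requests and surveys". Then: "After this 30-day period, they will complete additional baseline measures (T1) and then begin their assigned intervention, if applicable". The intervention lasts two months, which Table 1 places at days 31–90. On T2 the Overview says "After the interventions are delivered, participants will complete an additional self-report (T2"), and the footnotes to Table 2 define it as "T2: 3-month assessment".

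On the standing of the battery, Study Design says: "Additional assessments at baseline (T1), 3 months (T2), 6 months (T3), and 9 months (T4) will evaluate exploratory long-term outcomes". The same section takes HIV risk behaviors from breathalyzer results and daily self-reports. The data analysis plan counts them as days on which such behaviors occur. Its first goal is a "short-term analysis at the end of the 2-month intervention period", for which the short-term section compares the arms at T1 and T2 in a log-link count model with an exposure offset.

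**The concern.** Two separate problems arise from the one rule.

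- **T2 reaches behind the intervention.** Only about 60 days separate T1 and T2, but the T2 question looks back about 90. The reported count therefore mixes partners from the untreated run-in with partners from the treated period.
- **T1 is on another scale.** The T1 window is four times as long as the later ones. Distinct partners do not accrue in proportion to time (someone with a single stable partner reports one in either window), so neither the raw count nor a count per month puts T1 on the follow-up scale.

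At stake is the interpretability of this item. Number of partners is one of the four behaviors named in Aim 2, and in Table 2 this is the only measure described as a partner count over a period. The daily item asks about the past day and, as described, does not identify repeat partners, so summing it over days would count the same person more than once.

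**Working it through.** The plan states no figure for this item that could be reproduced. The check is overlap of the recall windows on the plan's own calendar, taking a month as 30 days.

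**Inputs.** Run-in days 1–30, T1 at about day 30 and intervention days 31–90 (Overview, Table 1). T2, T3 and T4 at about days 90, 180 and 270 (Study Design, Table 2 footnotes). Recall of 12 months at T1 and 3 months (90 days) later (Table 2). The participation timeline figure is not shown, but the text supports day 90 for T2.

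**Step 1: window overlap.**

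| Visit | Recall window | Days before intervention | Share |
|---|---|---|---|
| T2 | days 1–90 | 30 | 30/90 = 33.3% |
| T3 | days 91–180 | 0 | 0% |
| T4 | days 181–270 | 0 | 0% |

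Days 1–30 also lie inside the T1 window, so T1 and T2 overlap.

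**Step 2: attenuation at T2.** Assume a constant partner rate and full effect from day 31. The apparent rate ratio is (30 × 1 + 60 × RR)/90 = (1 + 2RR)/3.

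| True RR | Apparent RR at T2 | Share of log effect kept |
|---|---|---|
| 0.50 | 0.667 | 0.585 |
| 0.60 | 0.733 | 0.607 |
| 0.70 | 0.800 | 0.626 |
| 0.80 | 0.867 | 0.641 |
| 0.90 | 0.933 | 0.655 |

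On the 1 − RR scale exactly one third is lost. On the log scale about 59–66% is kept.

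**Step 3: does the attenuation need strict proportionality?** Take s stable partners plus r new partners per month, with the intervention acting on new partners only. The control count over 3 months is s + 3r. The treated count is s + r + 2r × RR at T2 and s + 3r × RR at T3. With assumed s = 1, r = 0.5 and RR = 0.70:

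- control: 1 + 1.5 = 2.5
- treated at T2: 1 + 0.5 + 0.7 = 2.2, ratio 0.88
- treated at T3: 1 + 1.05 = 2.05, ratio 0.82

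The reduction is 0.30 at T2 and 0.45 at T3. The ratios differ from Step 2, but the T2 reduction is still two thirds of that in a fully treated window.

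**Step 4: scale at T1.** In the same model with no change in behavior, T1 counts s + 12r and follow-up counts s + 3r (all values assumed).

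| s, r | T1 | Follow-up | Raw ratio | Per-month ratio |
|---|---|---|---|---|
| 1, 0.2 | 3.4 | 1.6 | 0.47 | 1.88 |
| 1, 0.5 | 7.0 | 2.5 | 0.36 | 1.43 |
| 1, 1.0 | 13 | 4 | 0.31 | 1.23 |
| 0, 0.5 | 6.0 | 1.5 | 0.25 | 1.00 |

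The raw count appears to fall by half or more. After division by window length it appears to rise by 23–88% whenever there is a stable partner. A window-length offset is right only in the last row.

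**Step 5: is the randomized contrast affected by T1?** With the same expected T1 count in each arm, the arm-by-time ratio at T2 is (treated T2/T1)/(control T2/T1) = treated T2/control T2. For s = 1, r = 0.5 this is (2.2/7)/(2.5/7) = 0.88, the same as the T2 arm ratio. The T1 window cancels.

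**The case against.** The strongest reply is about scope, and most of it stands. A reader might infer that Aim 2 as a whole is diluted. The documents do not support that. HIV risk behaviors are to be assessed from daily reports and modelled as days with risk behavior. Those reports have past-day recall and no overlap between run-in and treatment. The affected item is labelled exploratory and covers one of four behaviors, and the overlap arises at one of three follow-up visits.

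A reader might also infer that the 12-month T1 window biases the comparison of arms, or that the count model takes T1 as its reference level for this item. The first fails because the window is the same in every arm (Step 5). The second is not stated: the battery partner count is not in the list of modelled outcomes, and its analysis may be set out in a plan that is not at hand.

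The size can be challenged too. Step 2 assumes accrual in proportion to time, which the criticism of the offset denies, and full effect from day 31, although the four sessions are spread over a period of up to six weeks. So 0.80 is an illustration, not an established value. Step 3 shows that the direction does not depend on proportionality, and a later onset of effect would not remove the 30 untreated days.

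Finally, the 3-month recall has a merit. At T3 and T4 it covers days 91–150 and 181–240, when no monitoring takes place. A 2-month window at every visit would miss days 91–120 and 181–210, and a 30-day window would miss both gaps entirely. This is a good reason to leave T3 and T4 alone. It does not defend the T2 window or the unmatched T1 window.

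**Conclusion.** The point holds for the battery partner count only, as a modest flaw in a rule that the article itself fixes. About one third of the T2 recall window precedes the intervention, so the T2 between-arm contrast on this item is attenuated; 0.70 appearing as about 0.80 shows the order of magnitude under the stated assumptions. It also distorts the comparison of T2 with T3, since only T2 contains untreated time. Separately, change from T1 on this item cannot be interpreted, and T1 is a weaker baseline covariate than a matched window would give. The one-third share rests on T2 falling at about day 90 from study start.

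**What to change.** - **T2:** ask about partners since T1 (about 2 months), which brings the pre-intervention share from 33% to 0%.
- **T1:** add the same question for the past 2 months, to match T2, and for the past 3 months, to match T3 and T4. Keep the 12-month question for description only.
- **T3 and T4:** keep the 3-month recall, so that the unmonitored months stay covered.
- **If enrolment has already begun:** state that T1–T2 change in this item will not be interpreted as an intervention effect.

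The cost is one or two extra items at T1 and a T2 window that differs in length from T3 and T4, so T2 is compared with the 2-month T1 item and not directly with the later visits. The shorter T2 window will also give lower counts. The Discussion says that recruitment had not started as of February 2024; at that point this was a small questionnaire edit.

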###### HIV and STI Testing

At T1 and T4, participants will receive HIV and 3-site gonorrhea and chlamydia testing. We will use myLAB Box, with whom we have worked successfully in prior research, to deliver home testing kits to participants. myLAB Box is a fully laboratory-certified company using College of American Pathologists– and Clinical Laboratory Improvement Amendments–certified testing organizations and a HIPAA (Health Insurance Portability and Accountability Act)–compliant web interface [49]. The home testing kits include written instructions for how to collect the samples; participants will complete a finger prick blood sample for the HIV test and collect swab and urine samples for the gonorrhea and chlamydia testing. The test kits will be mailed by the participants to myLAB Box using prepaid shipping boxes. Before completing testing, participants will complete a HIPAA release form giving permission for their results to be shared with the study team. In the case of a positive test, the participant will have the opportunity to complete a telehealth visit (free of charge) with one of myLAB Box’s providers to discuss medications and linkage to care. The research team will also follow up with the participant to ensure that they have been connected to care and, in the case of a positive HIV test at T1, to communicate that they are no longer eligible to participate in the study.

###### Process Measures

We will assess several process measures related to the study app, including the number of opened and completed daily surveys, the number of messages opened, the length of time messages stayed open, the number of completed breathalyzer readings and location-based surveys, the frequency of missing GPS data, and the number of reported app issues. For each participant completing monitoring, we will generate a weekly report of these metrics to address any ongoing technical issues in a timely manner and to encourage the completion of surveys and breathalyzer readings if they are nonadherent. For the TRAC intervention, the interventionist will complete fidelity checklists after each session. We will also assess session attendance, dropout rates, and time spent in sessions. At the end of the intervention, we will conduct an overall fidelity assessment to aid in the interpretation of the intervention results. Overall, these process measures will inform future dissemination and implementation efforts.

###### Qualitative Intervention Assessment

At the T2 assessment, we will conduct a semistructured qualitative interview to obtain feedback on the SAM-only, and SAM+ TRAC, and SAM + TRAC-ER conditions. As applicable according to their intervention group, the interview will address the effects of the monitoring of alcohol use, attitudes toward MI intervention content, the impact of the EMI messages on drinking and HIV risk behavior, the impressions of intervention relevance and effects, challenges encountered during the intervention, and suggestions for improvement.

###### Participant Training

Participants in each condition will be trained to navigate the app and complete tasks, including completing location-based and daily assessments, reading messages, and providing breathalyzer readings. They will also be instructed on data safety and confidentiality procedures and how to remotely wipe their mobile phone data if it is lost or stolen. Wallet-size cards with information from the training and text reminders to carry the mobile phone and breathalyzers will be provided. A lack of response will be followed up with texts and telephone calls to ascertain the reason for noncompliance. If participants report problems, we will complete video calls to troubleshoot and further train participants, if needed.

###### Methods to Decrease Attrition and Missing Data

During the first 3 months of the study, participants will receive daily reminders to complete SAM, which will include information about potential incentives. Individuals in the SAM+TRAC and SAM+TRAC-ER arms will have weekly contact with research staff during the TRAC sessions and will receive reminders about upcoming appointments. We will contact participants 1 month before their follow-up monitoring periods to remind them about upcoming tasks and to ensure that contact information is up to date. The use of a novel smartphone app and a mobile breathalyzer, which has been highly rated by participants in past studies, will also help to ensure continued engagement with, and enthusiasm for, the study.

##### Ethical Considerations

All procedures were approved by the University of Kentucky Institutional Review Board (79109), with Yale University relying on the University of Kentucky for human participant oversight. All responses of participants will be held in confidence and kept secure. Only the researchers involved in this study and those responsible for the research oversight will have access to the information that may identify the participants.

All participants will complete informed consent before beginning research activities. All consenting procedures will be completed remotely and electronically using the REDCap (Research Electronic Data Capture; Vanderbilt University) *eConsent* framework. First, participants will be given basic information about the study. If they indicate interest in learning more and meet eligibility criteria after completing a brief screening survey, a member of the research team will contact them via their preferred contact method to confirm eligibility, provide more details about the research procedures, and obtain informed consent.

The research team will review all aspects of the study, including specific research procedures, the length of time participants will be enrolled in the study, and the associated risks and benefits of participation (eg, benefiting from free alcohol reduction counseling, which may impact overall health, and the risks of emotional distress from completing sessions and assessments and of a loss of confidentiality). Contact information for study staff, the principal investigators, the University of Kentucky’s Office of Research Integrity, and Yale University’s Human Research Protection Program will be provided, and the participant will be encouraged to contact any of the relevant individuals if they have questions or concerns regarding this research or to discuss their rights as a research participant.

If a participant chooses to sign up for the study after this conversation with the research team, they will complete consent by providing an electronic signature in REDCap. A copy of the consent form will be provided to the participant electronically and retained in REDCap’s file repository for study records. By signing this form, participants agree to allow for future use, and sharing of, their deidentified study data with other researchers, without additional informed consent. No participant will begin research procedures without first providing signed informed consent.

To protect confidentiality, participants will be assigned a unique study ID number. Any identifying information will not be stored alongside survey responses and will be permanently deleted after the completion of data collection in accordance with the University of Kentucky Institutional Review Board policies.

The research team will take all precautions to prevent a loss of confidentiality, one of the primary risks of this study. Data collected and stored on mobile phones are inherently less secure than other storage methods; however, participants will be advised on how to protect data stored on mobile phones, and study staff will be trained on best practices for securing information on mobile phones.

Electronic data will be stored and managed in REDCap and will be accessible only to authorized study personnel. All data collected through the mobile app will be hosted on a secure private server at Yale University. myLAB Box uses a HIPAA-compliant web portal that encrypts all medical information, and all communications sent by the company will minimize personal details. Due to the sensitive nature of HIV and STI results, we will give the test results a unique ID in addition to the study ID and maintain them in a separate REDCap database without other identifying information. Access to these, and all other study data, will be permitted only to authorized personnel, who will be trained in the areas of ethics, clinical trials, confidentiality protection, and human participant protection.

Participants can earn up to US $825 (US $685 for monitoring tasks and US $140 for assessments). All participants will receive a US $1 compliance payment for each breathalyzer sample submitted within a 90-minute period. They will also receive a US $1 payment for submitting their daily morning surveys. Thus, those who complete all monitoring tasks (all breathalyzer readings and daily self-reports) during the whole study (4 weeks before T1, 8 weeks during the intervention, and 4 weeks before T3 and T4) will receive US $685. Participants will also receive US $35 for completing the T1 assessment (US $20 for the questionnaire and US $15 for HIV and STI testing), US $25 for T2, US $30 for T3, and US $50 for T4. Escalating payments will be used to discourage study attrition.

While the compensation amount is relatively high, it is for activities completed across a full 9 months of participation. Total time spent on study activities ranges from 45 hours (SAM-only participants) to 50 hours (SAM+TRAC and SAM+TRAC-ER participants) when considering daily monitoring, assessments, time spent on screening and enrollment, and time spent in MI sessions. This results in an average compensation of US $16-$18 per hour in exchange for participation in study activities.

We will pay participants with reloadable debit cards, administered using OnCore clinical trial software (Advarra). Funds will be added to these cards as payments are earned, which then become immediately available. This system will allow for frequent payments without the burden of office visits or the delays from mailing checks.

